#### Primary aim analysis

As this is a pilot study, most data analysis will be exploratory, but based on best practices in the field to analyze clinical trial data. We will conduct an “intent to treat” analysis as the primary analysis approach. Baseline demographic characteristics will be explored to examine comparability between the groups. For continuous measures, we will explore average scores and distributions at each time point. To test for effects, we will use mixed-effects regression models (MRMs) to estimate average differences between outcomes on the standard vs. precision approaches using the scores on the acceptability, participant satisfaction, and home visitor-client relationship assessments. Specifically, we will add a dichotomous indicator for participants receiving the precision approach compared to the standard approach and examine the interaction of that dichotomous indicator with the change in outcome measure. The MRMs will include random effects at the individual and site levels to account for multiple time points within an individual and clustering by site. We will also examine the differences in proportion of participants who dropped out and who received 50% dosage using mixed effects logistic regression models accounting for clustering by site. For all analyses, we will report both unadjusted and adjusted analyses (adjustment based on differences in baseline demographics between the two groups at the *p <* 0.1 level). For all qualitative data, we will use thematic analysis to analyze interview transcripts using Dedoose software [37]. As transcripts are reviewed, “memos” will be generated to document initial impressions of topics and themes. Segments of transcripts will then be assigned codes based on a priori (i.e., from the interview guide) or emergent themes (i.e., open coding) [38].

All analyses for the secondary outcomes will be done on an exploratory basis only.

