This modularized approach to Family Spirit is called Precision Family Spirit. Precision Family Spirit was developed using mixed methods, including a secondary data analysis to identify meaningful subgroups that could inform how and when to tailor, and stakeholder workshops with program implementers (supervisors and home visitors) to identify core lessons, and lessons relevant to certain subgroups of clients [9, 16]. It consists of five lesson “pathways” that have been identified through formative work across Family Spirit’s national network of stakeholders [9]. There is a core set of lessons that every mother receives. For this pilot study, that means all Precision Family Spirit participants should receive 25 lessons from pregnancy to 12 months postpartum (the duration of enrollment). She receives additional lessons based on her emergent needs identified through data collection at home visits and at each assessment timepoint (Additional file 1). Thus, a Precision Family Spirit participant could be scheduled to receive between 25 and 41 lessons from pregnancy to 12 months postpartum. For example, if a participant is a first-time mother, she (and her family) will receive 6 additional baby care lessons (covering basic topics such as diapering and how to dress a baby) that are included in the Standard Family Spirit curriculum but may not be relevant for experienced mothers with previous children.

The study uses the Care4 implementation platform, which is a secure, HIPAA-compliant web-based application designed to capture data for the purposes of program implementation and evaluation [19]. Care4 is configured to notify home visitors when a participant needs to be added to any additional lesson pathways. Precision Family Spirit participants are assessed at each lesson visit using a measurement-based care approach [20–22] to understand and respond to emergent needs and help home visitors better track how their clients are doing over time. These short assessments are estimated to take 1–2 min to complete at each visit. Lessons are delivered in the same format as Standard Family Spirit, by trained home visitors in the home of the participant or a private place of their choosing.

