**Primary objectives**					
Acceptability	Program acceptability			X	X
	Qualitative interview**			X	X
Satisfaction	Participant satisfaction			X	X
	Qualitative interview**			X	X
Home visitor-participant relationship	Working alliance inventory: 1. Client WAI 2. Home visitor WAI		X	X	X
Retention	Participant tracking information collected throughout the duration of the pilot study				
Adherence					

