#### Primary outcomes

Our primary outcomes of interest include participant acceptability, satisfaction, quality of relationship between home visitor and client, retention, and adherence. Acceptability is measured from the perspective of the participant using a 15-item scale [16] administered at study midpoint and endpoint. Satisfaction is captured through a 34-item questionnaire used in the Family Spirit trials and adapted specifically for this study and administered at midpoint (around 6 months postpartum) and endpoint. All Precision Family Spirit participants are invited to participate in a short qualitative interview to further explore acceptability and satisfaction using an 11-item interview guide. In addition, we will explore home visitor acceptability and satisfaction through focus group discussions that follow a 9-item interview guide. The quality of the relationship between home visitor and client is captured using the short version of the Working Alliance Inventory (WAI) administered to both participant and home visitor. The WAI measures three domains of the relationship: goal alignment, task alignment, and bond. Retention is measured by comparing the number of participants who drop out in each study arm. Adherence is measured by comparing the percentage of retained participants in each study arm who completed their lessons as prescribed.

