#### Sample size calculation and statistical analysis

As this is a pilot study, our target sample (*N =* 60) was selected on the basis of feasibility of study completion, representativeness of the target study population (includes urban and rural sites) and with the desire to provide useful information to inform a fully powered research study (e.g., inclusion/exclusion criteria, variability in responses, estimated effects). Even so, with significance set to *a =* 0.05 and power set to 80%, using our *N =* 60 and accounting for 30% attrition, we would expect to be able to detect a large effect (*d =* 0.8) on continuous outcomes and a 35% difference in retention rates between the two groups.

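### The effect named for acceptability, satisfaction and working alliance is arm-by-change, which, with no pre-intervention score, is not the between-arm difference the plan sets out to estimate

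*Protocol article*

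**What the plan says.** All references are to the protocol article.

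- **Aim of the model (Primary aim analysis).** Mixed-effects models are to "estimate average differences between outcomes on the standard vs. precision approaches", "using the scores on the acceptability, participant satisfaction, and home visitor-client relationship assessments".
- **Term named (same section, next sentence).** An arm indicator is added, and the analysis will "examine the interaction of that dichotomous indicator with the change in outcome measure". Random effects for individual and site are included.
- **When the scales are measured.** Acceptability is assessed "using a 15-item scale [16] administered at study midpoint and endpoint"; satisfaction is "administered at midpoint (around 6 months postpartum) and endpoint". Table 2 confirms 6 and 12 months for both. For the relationship, Table 2 lists "Working alliance inventory: 1. Client WAI 2. Home visitor WAI" at 2, 6 and 12 months, with the baseline cell empty. Several secondary scales (depression, stress, quality of life, parenting knowledge) do have a baseline.
- **When exposure starts (Implementation strategy section).** The core schedule is that "all Precision Family Spirit participants should receive 25 lessons from pregnancy to 12 months postpartum (the duration of enrollment").
- **Detectable effect (Sample size section).** With N = 60, 30% attrition, alpha 0.05 and "power set to 80"%, the figure given is d = 0.8 between arms on continuous outcomes.

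**The concern.** The two consecutive sentences describe different quantities. One is a difference in level between arms; the other is a difference between arms in how the score moves over time. The two agree when the first measurement precedes treatment, because randomised arms then have the same expected starting value. Here the first acceptability and satisfaction scores come at 6 months, well into the allocated programme, so they already contain whatever effect the programme has had. For the WAI the first score comes at 2 months, which follows exposure for women enrolled in pregnancy.

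Aim 2 asks whether the two approaches differ on satisfaction, relationship and goal alliance, and the sample size statement is about a level difference. If the interaction were read as the effect, a benefit established by the first assessment and held would appear as no effect, and one that partly faded would appear to favour Standard. The pilot's estimates are meant to inform the size and design of a full trial, so the wrong coefficient could be carried forward.

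**Working it through.** **Inputs.** From the article: N = 60, 1:1 allocation by site, 30% attrition, so 60 × 0.7 = 42, or 21 per arm; d = 0.8; alpha 0.05; four sites, two per arm. Assumed, because the article does not give them: SD 1 at each visit, within-person correlation ρ of 0.3, 0.5 or 0.7, and site intraclass correlation (ICC) of 0 to 0.10. Tests are two-sided unless stated.

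**The plan's own figure.** A two-sample t-test with 21 per arm and d = 0.8 has 81.7% power one-sided and 71.6% two-sided. The stated 80% is therefore reproduced one-sided; the article does not state sidedness. Either way, d = 0.8 describes a difference in level, not in change.

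**What the interaction estimates.** Write d6 and d12 for the arm differences at 6 and 12 months.

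- Two visits (acceptability, satisfaction): interaction = d12 − d6. If d6 = d12 = d, it is 0 for every d.
- Three visits (WAI, linear time at 2, 6, 12 months): the slope weights are proportional to −4.67, −0.67 and 5.33, which sum to zero apart from rounding. A constant difference again gives 0.
- Waning benefit, 0.8 then 0.6: interaction = 0.6 − 0.8 = −0.2, in favour of Standard although Precision is better at both visits.

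These results are algebraic. They do not depend on ρ, sample size or clustering.

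**Power without clustering, two visits, 21 per arm.** Standardised effects:

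- interaction: (d12 − d6)/√(2(1 − ρ))
- average level: [(d6 + d12)/2]/√((1 + ρ)/2)

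At ρ = 0.5 the denominators are 1.000 and 0.866. For 0.8 at both visits, the average gives 0.8/0.866 = 0.924. Noncentral-t power:

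| Benefit at 6, 12 months | Interaction, ρ = 0.3 / 0.5 / 0.7 | Average level, ρ = 0.3 / 0.5 / 0.7 | Level at 12 months |
|---|---|---|---|
| 0.8, 0.8 | 5% / 5% / 5% | 88% / 83% / 78% | 72% |
| 0.4, 0.8 | 19% / 24% / 37% | 65% / 59% / 54% | 72% |

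A simulation (20,000 runs) agrees. With three visits and a constant 0.8, the interaction rejects about 5% of the time and the averaged difference has 93%, 88% and 81% power at the three correlations.

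**Power of the level contrast with sites allowed for.** At ρ = 0.5 the person-mean variance is (1 + 0.5)/2 = 0.75. With two sites per arm and total variance held fixed, Var(difference) = 2[(0.75 − ICC)/21 + ICC/2]. For a constant 0.8:

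| ICC | SE | Power, normal approximation | Power on 2 df (4 sites − 2 arms) |
|---|---|---|---|
| 0 | 0.267 | 85% (83% by t) | 39% |
| 0.02 | 0.299 | 76% | 33% |
| 0.05 | 0.342 | 65% | 27% |
| 0.10 | 0.402 | 51% | 22% |

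Clustering lowers the power of the level contrast but does not move the interaction away from zero under a constant benefit.

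**The case against.** A reader might infer that an early, sustained benefit would go unseen in this trial. The article does not support that. The arm indicator is in the model, average scores and distributions are to be explored at each time point, and the preceding sentence states the right aim. The level difference can be recovered from the same fit. What remains is that the article names the interaction, not the arm term, as what is examined. Moreover, if time is coded from the first visit, the arm term alone is the gap at that visit, not the average.

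A reader might also infer that every first score follows months of allocated programme. That is true of acceptability and satisfaction. It is not true of every WAI score: women may enrol with a baby up to 2 months old, so for late enrollees the 2-month WAI may fall near the start of study exposure. It is still not scheduled as a pre-intervention score.

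The strongest objection concerns the alternative. With four sites and no baseline on these scales, a level contrast absorbs stable differences between sites and home visitors, and the Limitations section concedes that the groups are unlikely to be fully comparable. A change contrast removes such stable differences. This stands, and it means that 83% must not be taken as the power of the replacement. It does not make the interaction an estimate of the difference that Aim 2 asks about.

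Finally, this is a pilot with mostly exploratory analysis, and a fuller analysis plan may name its contrasts. That limits the consequences, but the published wording would mislead if followed.

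**Conclusion.** The point holds as a mismatch between the stated aim and the named contrast for acceptability, satisfaction and both WAI ratings. With no scheduled pre-intervention score, the arm-by-change interaction measures only whether the gap moves between assessed visits. It is zero for a constant benefit of any size, and it points towards Standard when a benefit partly wanes. That part rests on algebra and the assessment schedule alone, with the qualification already made for late enrollees' first WAI.

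The size of the power contrast depends on assumptions. The figures of 5% against 83% hold for 21 per arm, ρ = 0.5, a constant 0.8 SD benefit and no site clustering. With sites counted, the second figure is well below 83%, and at most 39% on 2 df. The level contrast is the right target, but in this trial it is a pilot estimate to be read with its interval. Retention and dosage have separate logistic models and are outside the point.

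**What to change.** In the Primary aim analysis section, for acceptability, satisfaction and the client and home visitor WAI, name the arm difference in level as the effect. Estimate it from the same mixed model with visit as a category and the planned individual and site random effects. Report the 12-month contrast, with the 6-month contrast or the average over visits alongside, each with its confidence interval. Report the arm-by-time interaction as supporting information on whether the gap changes.

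State the limitation next to it: with four sites and no baseline on these scales, the level contrast carries between-site variance and pre-existing site differences.

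The cost is wording only, with the same data and the same type of model. It should be settled before outcomes are analysed, so that the choice of coefficient is not driven by the data.

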## Abstract

**Background:**

Home visiting is a well-supported strategy for addressing maternal and child health disparities. However, evidence-based models generally share implementation challenges at scale, including engagement and retention of families. Precision home visiting may address this issue. This paper describes the first known pilot randomized implementation trial of a precision home visiting approach vs. standard implementation. Primary aims are to: 1) explore the acceptability and feasibility of a precision approach to home visiting and 2) examine the difference between *Standard Family Spirit* and *Precision Family Spirit* on participants’ program satisfaction, client-home visitor relationship, goal alliance, and the impact of these factors on participant engagement and retention. Secondary aims are to explore potential differences on maternal behavioral and mental health outcomes and child development outcomes to inform sample size estimations for a fully powered study.

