### Randomization

Participating ITC of MI sites were randomized to use the Precision Family Spirit implementation strategy or Standard Family Spirit (control condition). Randomization occurred before recruitment began at the site level. The four sites were selected based on comparability of annual volume of clients served and geographic similarity (i.e., urban vs. rural). Once sites were matched, the study team flipped a coin to decide which sites would be assigned to each study arm. Participants are blind to whether they receive Standard Family Spirit or Precision Family Spirit as randomization occurs at the site-level. Thus, all participants at each site receive the same version of Family Spirit (standard or precision).

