#### Quality assurance

To ensure quality of participant consent procedures, all study staff have been certified to consent participants. Home visitors received initial in-person training on informed consent. Post-training, they had to demonstrate mastery of a full informed consent procedure with their supervisor prior to being certified. Program supervisors used a checklist to certify home visitors at their site.

Quality assurance of lesson delivery for both study arms occurs according to existing ITC of MI procedures. All home visitors are required to pass knowledge tests on each lesson prior to administering them to clients. Further, they must complete role plays and achieve a total average score of at least 3 out of 4 on a quality assurance form administered by a supervisor or program manager. To ensure ongoing high quality of lesson delivery, home visit observations are conducted at least biannually and ideally quarterly. For home visitors with at least 5 years of experience implementing Family Spirit, they are observed annually or more frequently if desired by the home visitor. Home visitors participating in this pilot trial are, in general, experienced in delivering Standard Family Spirit*.* Of 13 trained home visitors, 8 (62%) have at least 5 years of experience as Family Spirit certified home visitors. Further, 11 (85%) have at least 3 years of experience. All home visitors have been trained for at least a year before this pilot trial launched.

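### With four randomised sites, the mixed-model tests of arm effects need site-level degrees of freedom, and the resulting estimates are too imprecise to size the main trial

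*Protocol article*

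**What the plan says.** All references are to the protocol article.

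- **Allocation.** Under Trial design and Randomization, four sites were matched on client volume and urban or rural setting and allocated 1:1: "Once sites were matched, the study team flipped a coin to decide which sites would be assigned to each study arm". Two pairs is the natural reading, but the number of pairs is not stated.
- **Analysis.** Primary aim analysis presents mixed models as the means of testing effects on acceptability, satisfaction and the visitor-client relationship: "The MRMs will include random effects at the individual and site levels to account for multiple time points within an individual". The tested term is the interaction of arm with change in the outcome. Dropout and 50% dosage get mixed logistic models with site clustering. Neither a degrees-of-freedom method nor random slopes are mentioned. The section describes most of the analysis as exploratory.
- **Size.** "our target sample (*N =* 60) was selected on the basis of feasibility of study completion". The same paragraph then gives detectable differences of d = 0.8 and 35% in retention, "with significance set to *a =* 0.05 and power set to 80" percent, "accounting for 30% attrition".
- **Use of results.** That paragraph lists "variability in responses, estimated effects" among what the pilot should supply. The Abstract says outcome differences will be explored "to inform sample size estimations for a fully powered study".
- **Acknowledged limit.** Limitations notes the small number of groups, as a threat to comparability of the arms.

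**The concern.** Arm varies only between sites, so information about the arm effect comes from four units however many mothers are enrolled. A site random effect addresses this only if its variance is estimated adequately and the test uses a reference distribution suited to four clusters. With four sites the variance is often estimated as exactly zero, and the model then behaves as if mothers had been randomised individually.

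Two things are at stake. P-values and intervals may look more certain than the design allows. And an effect estimate dominated by site-to-site noise may be carried into the sample size of the main trial.

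**Working it through.** **Inputs.** From the article: N = 60, 30% attrition, four sites, two per arm, alpha 0.05, power 80%. Evaluable mothers: 60 × 0.70 = 42, or 21 per arm and 10.5 per site. The article gives no ICC, so 0 to 0.10 is assumed.

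**1. The article's own figure.** Treating mothers as independent, with 21 per arm, d = 0.8 has t-test power 0.716 two-sided and 0.817 one-sided. The stated 80% is thus reached only one-sided; sidedness is not given. For retention the control rate is not given. A 35-point difference has two-sided power of 0.79 to 0.82 with 30 per arm and control rates of 0.30 to 0.45. With 21 per arm it comes close to 80% only near 0.60 versus 0.95 (0.797). All these versions ignore site randomisation.

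**2. Degrees of freedom.** Four sites minus two arms gives 2 (critical t 4.30). Two pairs minus one gives 1 (critical t 12.71). The normal value is 1.96.

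**3. Type I error of a site random-intercept model.** REML simulation, one time point, equal sites of 10 or 15 mothers, no true arm effect:

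| Assumed site ICC | Wald z | t on 2 df | Site variance estimated as zero |
|---|---|---|---|
| 0 | about 4% | 5% | about 62% |
| 0.01 | about 5% | 5% | 58% to 59% |
| 0.05 | about 8% to 9% | 5% | 43% to 47% |
| 0.10 | about 10% to 12% | 5% | 31% to 37% |

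**4. Arm-by-change interaction.** If the site effect is an intercept only, it cancels from within-mother change, and site variation in change is not modelled. With design effect DE = 1 + (10.5 − 1) × ICC of change, type I error = 2 × [1 − Φ(1.96/√DE)].

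- ICC of change 0.05: DE = 1.475, giving 10.7%.
- ICC of change 0.10: DE = 1.95, giving 16.0%.

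**5. Precision and power on 2 df.** Half-width in SD units = 4.303 × √(2/21 × DE):

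| Assumed ICC | DE | 95% half-width | Power at d = 0.8 |
|---|---|---|---|
| 0 | 1.000 | 1.33 SD | 0.32 |
| 0.05 | 1.475 | 1.61 SD | 0.24 |
| 0.10 | 1.950 | 1.85 SD | 0.20 |

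The difference detectable with 80% power on 2 df is d = 1.7 at ICC 0 and 2.4 at ICC 0.10, against the stated 0.8.

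**The case against.** The strongest reply is that the article fixes no degrees-of-freedom method and that such detail normally belongs in an analysis plan. This stands in part. With Satterthwaite-type degrees of freedom the same model has type I error of only about 3% to 7% over ICC 0 to 0.10, and even Wald z is sound when the ICC is near zero. The excess in the table is therefore conditional on normal-theory inference and a moderate ICC. Likewise, the interaction figures hold only if the site effect is an intercept only, which the article does not say.

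The article also calls most of its analysis exploratory, uses 0.05 only in the detectable-effect sentence, and discloses the four sites. That softens the point. It does not remove it, because Limitations treats few sites as a comparability problem and not as a limit on inference or on planning use.

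Stronger readings that a reader might infer are not supported:

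- **That no test can be valid.** A 2-df t-test holds 5%; what it lacks is precision. Two matched pairs allow only four allocations, so a two-sided randomisation p-value cannot fall below 2/4 = 0.5, but no randomisation test is planned.
- **That the pilot is meant to supply an ICC.** No section mentions one.
- **That the pilot cannot give effect estimates.** It gives them, imprecisely.
- **That omitting home visitors invalidates the arm comparison.** The article counts home visitors ("Of 13 trained home visitors, 8 (62%) have at least 5 years of experience"), and the working alliance is rated by both client and visitor, so clustering by visitor is plausible. But if visitors are nested in sites, site-level inference already absorbs it. A visitor term is a secondary matter.

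**Conclusion.** The point holds as one about reference distribution, precision and use of results. Under Wald z inference the nominal 5% becomes about 8% to 9% at site ICC 0.05 and 10% to 12% at 0.10. Under valid 2-df inference, an interval of ±1.3 to ±1.9 SD cannot distinguish a large benefit from none or from harm, so the pilot effect is not a sound basis for sizing the main trial. The d = 0.8 and 35% statement describes individually randomised mothers, not this design.

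The figures rest on assumed ICCs, equal site sizes, normal outcomes and a single time point. The 2-df results set the pairing aside; respecting it leaves 1 df and wider intervals. The change should be made, but it does not put the pilot's feasibility aims in doubt.

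**What to change.** - **Primary aim analysis.** Replace the wording about testing effects with estimation. Report arm differences with 95% intervals on site-level degrees of freedom (t with 2 df on site summaries, or an equivalent small-sample correction), for binary outcomes too. Show the four site values and the two within-pair differences descriptively. Make no 0.05-level claim.
- **Sample size paragraph.** Qualify the d = 0.8 and 35% statement as ignoring randomisation by site.
- **Planning of the main trial.** State that it will be sized on a minimum important difference and an external or assumed ICC range, taking only SDs, retention and completeness from the pilot.
- **Optional.** As a sensitivity analysis, add a home-visitor random intercept for satisfaction and working alliance.

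The change is to wording and reporting; design and data collection stay as they are. The price is much wider intervals and no claims of significance.

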### Standard Family Spirit

Mothers at the control sites receive Family Spirit as usual, per existing ITC of MI program policies and procedures. In the standard of care, families receive regular home visits, delivered in the same sequence until 3 years postpartum (63 lessons total). Because the duration of enrollment for this pilot study is from pregnancy to 12 months postpartum, Standard Family Spirit participants should receive 47 lessons total. Home visitors at Standard Family Spirit sites use the Care4 platform to track their clients. They receive notifications about high depression scores, risk of self-harm, and potential domestic violence issues, but they do not receive notifications about other risk categories (first-time mom, substance use, nutrition, sexual and reproductive health) that would inform tailoring sequences in the Precision Family Spirit implementation approach. Details on the rationale for selecting these risk categories have been described elsewhere [9, 16].

In both arms of the study, home visitors provide referrals and connections to community agencies and services as needed. Existing procedures are in place to link participants to assistance that is available in their area. Home visitors often act as navigators and advocates for the families they serve. In addition, participant transportation to and from doctor and clinic appointments is common and will continue for enrolled participants in each arm.

The study team recognizes that differences may be small regarding number of prescribed lessons between Precision Family Spirit and Standard Family Spirit participants, but implementation outcomes may be potentially detectable because we are measuring program participant acceptability, satisfaction, quality of relationship between home visitor and client, retention, and adherence.

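### Lesson dose is tested only as a yes/no at 50%, and adherence only as completed or not; each mother's share of scheduled lessons should be the main dose analysis

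*Protocol article*

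**What the plan says.** Two sections of the protocol article fix how lesson dose is handled.

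- Primary outcomes: "Adherence is measured by comparing the percentage of retained participants in each study arm who completed their lessons as prescribed". This is a yes/no per mother, among retained mothers only.
- Primary aim analysis: "We will also examine the differences in proportion of participants who dropped out and who received 50% dosage using mixed effects logistic regression models". The sentence goes on to say that clustering by site is accounted for, and the section makes intent to treat the primary approach.

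The underlying count has a wide range. In the control arm, "Standard Family Spirit participants should receive 47 lessons total" by 12 months postpartum. The section on the Precision strategy gives 25 core lessons and up to 41 in all, depending on needs found over time.

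The mixed-effects regression on scores in Primary aim analysis covers acceptability, satisfaction and the home visitor-client relationship. Lesson dose is not among them.

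On size, the sample of 60 "was selected on the basis of feasibility of study completion", and was also meant to inform a full trial on variability in responses and estimated effects. The section adds that, "accounting for 30% attrition", "we would expect to be able to detect a large effect (*d =* 0.8) on continuous outcomes". It gives no power figure for dose or adherence.

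**The concern.** Engagement, retention and adherence are what the implementation strategy is meant to change (Table 1). Half of 47 lessons is 23.5. Under the cut, a Standard mother with 24 lessons scores the same as one with 47, and a mother with 23 scores the same as one with none. A rise from 60% to 80% of lessons among mothers already past half cannot show in the planned test. The other primary outcomes measured on a scale keep that scale in the model, so consistency does not require the cut.

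Two things are at stake. The first is estimation: a pass rate gives neither the mean share of lessons nor its SD, and a pilot that feeds a sample size calculation needs both. The second is sensitivity: cutting a graded measure in two usually loses power, by an amount that depends on the shape of the dose distribution.

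**Working it through.** **Inputs.** From Sample size calculation: N = 60, alpha 0.05, 80% power, 30% attrition, d = 0.8 for continuous outcomes, 35 points for retention. From Trial design: four sites, 1:1. Not given, so assumed: the shape of the dose distribution, the share of mothers passing 50%, the ICC, and whether the test is one- or two-sided.

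**The plan's own figures.** 60 × 0.7 / 2 = 21 per arm. For a t test, the noncentrality is d√(n/2) = 0.8 × √10.5 = 2.59. Power is 81.7% one-sided and 71.6% two-sided. For retention of 50% against 85%, power at 21 per arm is 79.9% one-sided and 69.1% two-sided. The stated figures therefore reproduce one-sided, without clustering. I use two-sided 0.05 below and note the one-sided result.

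**Number per arm.** A mother who leaves early still has a lesson count, so an analysis of all enrolled mothers has 30 per arm. Then 0.8 × √15 = 3.10 and full-scale power is 86.1%.

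**After the cut, normal dose, independent mothers.** If a share p1 of control mothers passes, then p2 = Φ(Φ⁻¹(p1) + 0.8). With p̄ the mean of p1 and p2,

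power = Φ{[(p2 − p1) − 1.96√(2p̄(1 − p̄)/n)] / √([p1(1 − p1) + p2(1 − p2)]/n)}.

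For p1 = 0.50 and n = 30: p2 = 0.788, p̄ = 0.644, and (0.288 − 0.242)/0.118 = 0.39, so power is 65%.

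| Control passing | Precision passing | Power, formula | Power, simulated tests |
|---|---|---|---|
| 30% | 60.9% | 68% | 69% |
| 50% | 78.8% | 65% | 65-67% |
| 70% | 90.7% | 53% | 53-57% |

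The loss is 86 − 69 = 17 to 86 − 53 = 33 points. At 21 per arm the simulated figures are 72% against 40-52%. One-sided at 30 per arm, with 50% to 80% of all mothers on one side of the cut, power is 92% against 66-79%, a loss of 13 to 27 points. A more lopsided cut costs more: with 90% of mothers on one side, two-sided power is 36%.

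**Respecting the four sites.** Take two sites of 15 per arm and a t test on site means with 2 df. The arm difference has SE √(ICC + (1 − ICC)/15) in SD units.

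- ICC 0.01 (assumed): SE = √0.076 = 0.276, noncentrality 2.90, full-scale power 37%. Simulated power after the cut is about 22-28%, a loss of 8 to 14 points.
- ICC 0.05 (assumed): SE = √0.113 = 0.337, noncentrality 2.38, full-scale power 28%. Simulated power after the cut is about 19-24%, a loss of 4 to 8 points.

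**Non-normal dose, simulated, 30 per arm, no clustering, assumed rates.**

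- Dropout and attendance both differ (retention 50% against 70%, attendance while enrolled 60% against 75%): 82% full-scale against 66% cut.
- Only dropout differs, spread over time (50% against 85% retained, attendance 70% in both arms): 56% against 48%.
- Only dropout differs, with leavers very low and stayers very high: t test minus cut runs from about 0 to +3 points (−3 to 0 at 21 per arm). A rank test is 8 to 14 points weaker than the cut.

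**The denominator.** Half of the prescribed lessons is 23.5 in Standard and 12.5 to 20.5 in Precision. A Precision mother who leaves after 15 lessons has 15/25 = 60% of the core lessons but 15/41 = 37% of the maximum. Her status under the 50% cut already depends on a rule that the article does not state.

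**The case against.** The strongest reply is that power is a poor yardstick here. The sample was set by feasibility, most analysis is called exploratory, and with two sites per arm between-site variation limits the dose test more than the cut does. This stands, and it is why the firmer ground is estimation.

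It can also be said that the documents present the problem as families leaving, and that a dose shaped by dropout loses little at a 50% cut. That stands for that scenario. But Primary aim analysis already tests dropout on its own. What a dose analysis adds is attendance among mothers who stay, and that is where the cut hides most.

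Three stronger readings are tempting and should not be drawn:

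- That the planned test loses 17 to 33 points. That range ignores the clustering which the planned model includes.
- That the article says every lesson is recorded. It says that participant tracking runs throughout and that both arms use Care4. Recording by lesson is an inference, though a safe one, since neither yes/no measure can be scored without completed and prescribed lessons.
- That the mean and SD of dose will never be reported. The article plans to explore averages and distributions of continuous measures, and a fuller document may include dose there. The point is narrower: the dose test that the article fixes does not deliver them.

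**Conclusion.** The point holds in a limited form. The article fixes dose and adherence as yes/no measures, gives no reason for the 50% cut, and names no full-scale dose analysis. The planned dose test therefore cannot supply the mean share, SD or graded effect that a full trial would be sized on.

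The 17 to 33 point loss is conditional on a roughly normal dose, d = 0.8, two-sided 0.05, 30 independent mothers per arm and 30% to 70% of control mothers passing. Only d = 0.8 comes from the article, and there it refers to continuous outcomes in general. Once the sites are respected, the loss is about 4 to 14 points at assumed ICCs of 0.01 to 0.05. None of this invalidates the pilot. It is a specific, inexpensive improvement that serves the pilot's stated purpose.

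**What to change.** In Primary aim analysis, make the main dose analysis each enrolled mother's lessons completed, as a share of the lessons that her arm and pathway schedule from her enrolment point to 12 months postpartum. Enrolment may fall in pregnancy or up to 2 months after birth, so the starting point matters.

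Fix the denominator rule in advance and apply it in the same way to mothers who leave early. Otherwise a Precision mother who leaves before extra lessons are assigned gets an inflated share. Raw counts will not do, because prescribed totals differ by arm.

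Use a linear or overdispersed binomial mixed model with the site term already planned. Report the arm difference in mean share with its confidence interval, and the SD. A rank test should not be the main method, since it can be weaker than the cut when dropout drives dose.

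Keep 50% dosage and completion as prescribed as supporting percentages, and state that the first covers all enrolled mothers and the second only retained mothers.

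The cost is a few lines of analysis text and, on the inference above, no new data. A mean share is slightly harder to communicate, the skewed distribution needs a check, and the denominator must be defined, which the 50% cut already requires.
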